#### Intent-to-treat sample and intervention non-compliance

Analyses will use the standard intent-to-treat (ITT) approach to examine the effect of the TMI Adjunct condition relative to the Standard Care Alone condition. Our ITT approach will analyze participants as belonging to the group they were randomized to, regardless of their compliance, because excluding those who do not use the TMI would bias results in favor of the TMI condition, increasing the probability of type I errors [56].

#### Preliminary analyses

Although participants will be randomly assigned (in groups of about 5–7 individuals) to either the TMI Adjunct or Standard Care Alone conditions, imbalance between the two groups on some of the baseline characteristics may occur. However, since assignment to treatment condition is random, any differences that arise are due to random chance [57, 58]. We will present balance tables of baseline data to confirm the two groups are similar. In all relevant analyses, we will control for variables that are expected to predict the outcome by including them as covariates in the models.

#### TMI feasibility and acceptability

Measures of TMI feasibility will include the percent of text messages that were delivered to the correct individual, in the correct sequence, and with appropriate responsiveness to each participant’s replies [59]. Measures of TMI acceptability will include percentages of participants who chose to stop receiving text messages, who continued to engage with the program (assessed by periodic prompts throughout the 6-week period to determine whether they were reading the messages), and who completed requested responses to the text messages [59]. At the 3-month follow-up, TMI participants will also complete survey items to obtain their feedback on text frequency, text content, ease of using the TMI, and whether they had trouble receiving texts in a timely fashion [60].

### Effects of the TMI on smoking behavior

The primary goal of analyses is to assess the promise of the TMI as an adjunct to standard brief cessation counseling and obtain preliminary estimates of intervention effect sizes for a larger trial of the TMI with homeless young people. Given the proposed small sample size, sophisticated modeling that makes adjustments for multiple covariates or potential non-response bias might not be possible; therefore, some analyses will be primarily descriptive.

Biochemically-verified 7-day point prevalence quit rates and self-reported continuous abstinence at 3-months following the baseline visit will be analyzed separately using logistic regression. Logistic regression will also permit modeling the effects of potentially important covariates (e.g., education, age, gender, nicotine dependence, smoking history). We will also compare average number of days smoked by comparing the 30 days immediately prior to the smoking cessation counseling session to the 30 days after the participant’s target quit date. We will fit a regression model to explain the difference in pre and post-intervention outcome by the randomization group indicator (TMI Adjunct vs. Standard Care Alone). We will also estimate a difference in differences (DID) approach for this outcome, including time (a dummy variable indicating pre- versus post-period), the intervention group indicator, and their interaction, and a random subject effect to properly account for the correlation of the repeated measures on each subject and produce efficient estimates of the intervention effect.

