Enrolled participants will complete their baseline survey while waiting for the 30-min group-based smoking cessation counseling session to start. After the counseling session, participants randomized to the TMI condition will begin receiving 6 weeks of text messages to their personal cell phone. Three months after the baseline survey, all participants will receive a follow-up survey. We expect a very high retention rate at 3-month follow-up based on the 91% retention rate we achieved at 3-month follow-up in a recent evaluation of a substance use and sexual risk reduction program involving 200 homeless young people conducted at some of the same study sites participating in this project [38]. We will use a number of innovative retention procedures that have helped us limit attrition with this transient population, such as collecting tracking information on their hangouts, places used for sleeping outdoors, and social networking sites; see our previous work for a detailed description of these procedures [39]. Figure 1 shows participant flow through the study, and Fig. 2 contains a SPIRIT (Standard Protocol Items: Recommendations for Interventional Trials) flow diagram of the RCT schedule of enrollment, interventions, and assessments.

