### Analytic plan

Data will be collected from participants using self-administered paper–pencil surveys, with the survey response forms then scanned and checked for accuracy.

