### Measures

Our primary and secondary smoking-related treatment outcomes are based on recommendations by the Society for Research on Nicotine and Tobacco [61]. The primary treatment outcome will be continuous abstinence, defined as no smoking from the target quit date through the 3-month follow-up. The secondary treatment outcome will be biochemically-verified 7-day point prevalence abstinence at the 3-month follow-up, with participants who report that they are abstinent having their status confirmed via expired air carbon monoxide (CO) using a CoVita Smokerlyzer ^®^ monitor and, in cases where the breath sample suggests that they are currently smoking, by saliva cotinine using a NicAlert cotinine test strip. Participants who report no smoking, but whose CO level > 5 ppm or cotinine level > 10 ng/mL, will be coded as smoking. We acknowledge that there is a possibility of carbon monoxide false positives related to smoking other substances such as marijuana. We will probe further about marijuana use if a participant reports no smoking but biochemical data suggest otherwise [62]. In addition, we will utilize the reliable and valid smoking time line follow-back (TLFB) procedure [63] to collect detailed information on smoking patterns in the 30 days prior to the cessation counseling session (assessed at baseline) and the 30 days after the participants’ target quit date (assessed at follow-up). This will be used to examine intervention effects on the average number of cigarettes smoked per day.

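### As written, a participant can be a primary-outcome success on self-report and be coded as smoking by the biochemical test at the same follow-up

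*Protocol article*

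**What the plan says.** Two sections of the Protocol article fix the smoking outcomes.

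- *Measures* (the section on smoking outcomes) ranks them: "The primary treatment outcome will be continuous abstinence, defined as no smoking from the target quit date through the 3-month follow-up". It continues: "The secondary treatment outcome will be biochemically-verified 7-day point prevalence abstinence at the 3-month follow-up". Those who report abstinence give a breath sample for CO, followed by a saliva cotinine strip if the breath result points to smoking. The coding rule is: "Participants who report no smoking, but whose CO level > 5 ppm or cotinine level > 10 ng/mL, will be coded as smoking". The section concedes that "there is a possibility of carbon monoxide false positives related to smoking other substances such as marijuana" and promises further questions about marijuana, without saying whether the answers alter the coding.
- *Effects of the TMI on smoking behavior* says how the two are analysed: "Biochemically-verified 7-day point prevalence quit rates and self-reported continuous abstinence at 3-months following the baseline visit will be analyzed separately using logistic regression".

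Three other places bear on the point.

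- *Analytic plan*: data come from "self-administered paper–pencil surveys".
- *Recruitment and follow-up procedures*: after counselling, "participants randomized to the TMI condition will begin receiving 6 weeks of text messages to their personal cell phone". No sham texts are described for standard care, and blinding is not mentioned.
- *Missing Data and Attrition*: the sensitivity analyses there deal with non-response, not with false reports from people who do respond.

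**The concern.** The primary outcome rests on self-report alone, although an objective result from the same follow-up will be in hand for the very people whose claim matters. Nothing says that a failed test overrides a claim of continuous abstinence. The article could therefore report the same person as abstinent on the primary outcome and as smoking on the secondary.

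At stake is the effect estimate. The stated goal of the analyses is to judge the promise of the TMI and to obtain preliminary effect sizes for a larger trial. If false claims were more common in the TMI arm, the primary estimate would favour the TMI without any real benefit. If they were equally common in both arms, a real benefit would look smaller than it is. TMI recipients know that they are getting texts, and some sample texts encourage them to think of themselves as nonsmokers, so a difference between arms is conceivable.

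**Working it through.** **1. Who is tested, and what a failed test changes**

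- Primary success requires a claim of no smoking from the target quit date through the 3-month follow-up. Table 2 puts the TMI quit day on day 3 of the programme, so the last 7 days before follow-up lie well inside that interval.
- Anyone making this claim therefore also claims 7-day abstinence, and belongs to the group that *Measures* sends for CO testing.
- Suppose such a person has CO above 5 ppm. On the verified 7-day outcome the coding is smoking. On the primary outcome, described as self-reported and analysed separately, the coding is abstinent. No sentence expressly removes the second coding.

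This step is logical and needs no assumed rate.

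**2. The plan's own figures** (*Power Considerations*)

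- Effective sample size: 36/(1 + 5 × 0.05) = 28.8 per condition, as stated.
- Power at h = 0.72, two-sided alpha 0.05: Φ(0.72 × √(28.8/2) − 1.96) = 78.0%, close to the stated 80%.

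The endpoint problem does not depend on these figures. They set the scale for step 4.

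**3. Over-reporting that differs by arm** (assumed rates, no true effect)

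Observed rate = p + (1 − p) × f, where p is true abstinence and f is the share of continuing smokers who falsely claim abstinence. With p = 10% in both arms:

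| f, standard care | f, TMI | Observed rates | Relative gain | Odds ratio |
|---|---|---|---|---|
| 0% | 5% | 10% vs 14.5% | 45% | 1.53 |
| 0% | 10% | 10% vs 19% | 90% | 2.11 |
| 5% | 5% | 14.5% vs 14.5% | 0% | 1.00 |
| 5% | 10% | 14.5% vs 19% | 31% | 1.38 |
| 5% | 15% | 14.5% vs 23.5% | 62% | 1.81 |
| 5% | 20% | 14.5% vs 28% | 93% | 2.29 |

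First row in full: 0.10 + 0.90 × 0.05 = 0.145; odds ratio (0.145/0.855)/(0.10/0.90) = 1.53.

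In people, with 36 per condition followed up: 36 × 0.90 = 32.4 smokers, so 5% is 1.6 false claims and 10% is 3.2.

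With f = 5% in standard care, an effective size of 28.8 per arm and p from 5% to 15%, the chance of a false positive at nominal 5% is 7–9%, 12–18% or 20–31% when f in the TMI arm is 10%, 15% or 20%.

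**4. Equal over-reporting, true h = 0.72, control abstinence 10%**

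| f in both arms | Observed h | Power |
|---|---|---|
| 0% | 0.72 | 78% |
| 5% | 0.64 | 69% |
| 10% | 0.58 | 60% |
| 20% | 0.49 | 46% |

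The false-positive rate stays at 5%, but the effect estimate shrinks.

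**The case against.** The strongest reply is that the coding rule in *Measures* is a sentence of its own, not expressly limited to the secondary outcome. Someone coded as smoking at follow-up cannot have been smoke-free through follow-up, so the rule could be read as covering both outcomes. That reading is possible. It conflicts, however, with the analysis section, which sets a self-reported outcome against a verified one. On either reading the two sections need the same clarifying sentence.

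A second reply is that the verified outcome is already prespecified and modelled in the same way, so any divergence will be visible, and that this is a pilot with partly descriptive analyses. This limits the harm. It does not justify leaving the contradiction in the outcome ranked first.

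A reader might go further and infer any of the following, which the documents do not support:

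- *Over-reporting is likely to favour the TMI.* No misreporting rate is given, and blinding is never mentioned. Both arms receive counselling, patches and a quit date, so both may feel pressure to report success. The nonsmoker-identity texts are examples from a pool of 174, a SLIP keyword invites people to admit smoking, and the texts stop at 6 weeks while the outcome is taken at 3 months.
- *Any modest misreporting would equal the 50–60% gain that the Background cites for TMIs.* That figure is a relative gain in quit rates and should not be set against odds ratios. On its own scale, 14.5% against 10% is 45%, below the cited range. Only the larger scenarios reach or pass it.
- *A failed test proves smoking.* The article concedes CO false positives from marijuana, and its either-or rule codes a raised CO as smoking even when cotinine is low.

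**Conclusion.** The point stands in a limited form. On the plain reading, the primary outcome is unverified self-report, and a failed test at the same follow-up does not touch it. A primary success can therefore be coded as smoking. This follows from the text and rests on no assumed rate.

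The size of any bias is unknown. In the illustrations at 10% true abstinence, an excess of 5 to 10 percentage points in false claims among TMI smokers produces spurious odds ratios of about 1.4 to 2.1, depending on the control-arm rate. Equal over-reporting of 5% to 20% lowers power for the planned effect from 78% to between 69% and 46%. All misreporting rates, and the 10% abstinence, are assumptions. That over-reporting differs by arm is plausible but not shown.

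The change should be made because the effect estimate is meant to inform a larger trial and the correcting information is already being collected.

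**What to change.** - Define primary success as self-reported abstinence from the target quit date through the 3-month follow-up that is not contradicted by the CO/cotinine check already planned at that follow-up. Code claimants who are contradicted as not abstinent.
- Amend *Effects of the TMI on smoking behavior* and *Measures* so that both describe the primary outcome this way.
- State how a claimant without a usable sample is coded. State also how a raised CO with a low cotinine, or with reported marijuana use, is handled, and apply the same rule to both outcomes.
- Report unverified self-reported continuous abstinence as a sensitivity analysis.

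The cost is small but not nil. No extra samples, visits or participants are needed. The primary quit rate may fall, and some true abstainers may be misclassified through CO false positives. The test detects only recent smoking, so it can contradict a claim of three months' abstinence but cannot prove one, and concealed earlier lapses will remain.

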#### Effects of the TMI on other smoking-related outcomes

As a secondary focus, we will examine estimates of the intervention effect on proximal outcomes/mediators (i.e., factors associated with smoking and motivation to quit among young people experiencing homelessness [9] and areas of focus in the TMI) and assess trends. While the planned sample will not be large enough for detecting statistically significant mediation effects, it will allow us to produce estimates of the intervention effect on proximal outcomes/mediators and assess trends. We will adopt a similar modeling approach to the one just described, using a DID approach, since these variables will be measured at both baseline and follow-up.

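### The reduction outcome is days smoked in one section and cigarettes per day in another, and the stated change-score and DID models leave out the baseline value as a covariate

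*Protocol article*

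**What the plan says.** All references are to the protocol article.

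- **Outcome, analysis section** (Effects of the TMI on smoking behavior): "We will also compare average number of days smoked by comparing the 30 days immediately prior to the smoking cessation counseling session", set against the 30 days after the target quit date.
- **Outcome, Measures section on smoking outcomes**: time line follow-back data are collected for the same two windows, and "This will be used to examine intervention effects on the average number of cigarettes smoked per day".
- **First model**: "We will fit a regression model to explain the difference in pre and post-intervention outcome by the randomization group indicator".
- **Second model**: "We will also estimate a difference in differences (DID) approach for this outcome", with time, group, their interaction and a random subject effect. It is said to "produce efficient estimates of the intervention effect".
- **Mediators** (Effects of the TMI on other smoking-related outcomes): "We will adopt a similar modeling approach to the one just described, using a DID approach". These variables are measured at baseline and follow-up.
- **Covariates** (Preliminary analyses): "In all relevant analyses, we will control for variables that are expected to predict the outcome by including them as covariates in the models". The analysis section adds that "sophisticated modeling that makes adjustments for multiple covariates or potential non-response bias might not be possible". Neither sentence names the baseline value of the outcome.

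**The concern.** There are two linked problems.

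First, one instrument and one pair of windows yield two different outcomes. Days smoked is not listed as a measure, and cigarettes per day has no stated analysis. The two can disagree: someone who goes from 20 to 3 cigarettes on every day of the month shows no change in days smoked. The overview asks whether the TMI gives greater reductions in smoking, so the outcome closest to that question should have one definition, or two in a fixed order. Otherwise the choice stays open until the data are seen.

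Second, a change score fixes the slope of follow-up on baseline at 1 instead of estimating it. The pilot exists to supply effect and variability estimates for a larger trial, so precision that can be had from data already collected is worth having. Because the DID is carried over to all mediators, the choice affects many estimates.

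**Working it through.** **1. The plan's own figure.** The Power Considerations section gives 36/(1 + 5×0.05) = 28.8 effective participants per condition, which is correct. At that size and two-sided alpha 0.05 (sidedness is not stated), power for h = 0.72 is 78.0%, close to the stated 80%. Exactly 80% needs h = (1.960 + 0.842)×√(2/28.8) = 0.738. This concerns quit rates and does not depend on the point made here.

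**2. Are the two models different?** In one simulated complete data set (36 per condition, baseline SD 4, residual SD 3.5, slope 0.5, all assumed), the results were:

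| Model | Estimate | SE |
|---|---|---|
| Change score on group | −1.154 | 0.915 |
| DID, random subject effect | −1.154 | 0.915 |
| Follow-up on group and baseline | −1.735 | 0.779 |
| Change score on group and baseline | −1.735 | 0.779 |

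The first two coincide. The last two also coincide, so what matters is the baseline term, not whether the response is the follow-up value or the change.

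**3. Precision.** Let s0 and s1 be the baseline and follow-up SDs and rho their correlation. The per-person variances, in large samples, are:

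- change score or DID: s1² + s0² − 2·rho·s0·s1
- baseline-adjusted: s1²(1 − rho²)

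The difference is (s0 − rho·s1)², which is never negative and is zero only when s0 = rho·s1. With s0 = s1 the ratio, adjusted over change score, is (1 − rho²)/(2(1 − rho)) = (1 + rho)/2. The document gives neither rho nor the SDs, so both are assumed:

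| s0/s1 | rho 0.3 | rho 0.5 | rho 0.7 |
|---|---|---|---|
| 0.25 | 0.997 | 0.923 | 0.716 |
| 0.30 | 1.000 | 0.949 | 0.761 |
| 0.75 | 0.818 | 0.923 | 0.995 |
| 1.00 | 0.65 | 0.75 | 0.85 |
| 1.25 | 0.502 | 0.571 | 0.628 |

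With equal SDs, the difference detectable with 80% power at 28.8 per condition, in follow-up SD units, is (1.960 + 0.842)×√(2V/28.8), where V is the variance above with s1 = 1:

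| rho | Change score or DID | Baseline-adjusted |
|---|---|---|
| 0.3 | 0.874 | 0.704 |
| 0.5 | 0.738 | 0.639 |
| 0.7 | 0.572 | 0.527 |

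Ignoring baseline altogether gives 0.738, so with equal SDs and rho below 0.5 the change score does worse than not using baseline at all.

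**4. Which row applies to which outcome?** Eligibility requires smoking on at least 20 days in the past month, so baseline days lie between 20 and 30 and their SD cannot exceed 5. Follow-up days can run from 0 to 30. A ratio s0/s1 of 0.25–0.30 is therefore a reasonable assumption for days smoked. Cigarettes per day and the mediators have no comparable limit on the high side at baseline, so ratios nearer 1 are plausible for them.

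A simulation at 36 per condition, under assumed distributions and without clustering, agrees:

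| Outcome | Correlation | s0/s1 | Variance ratio |
|---|---|---|---|
| Cigarettes per day | 0.17–0.55 | about 1.0 | 0.58–0.78 |
| Days smoked | 0.14–0.43 | 0.31 | 0.98–1.02 |

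**The case against.** The strongest reply is that the precision argument misses the outcome to which the article attaches its model. The change score is stated for days smoked, and for that outcome the gain may be close to nil. This stands. A reader might take a 15–35% variance reduction to apply to the quoted analysis; the eligibility limit on baseline days does not support that.

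Three other strong readings also fail.

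- *Days smoked cannot show a reduction.* It can: a baseline near the ceiling leaves the whole range below for a fall after the quit date. What it misses is lower intensity on days still smoked.
- *The change score over-corrects chance imbalance.* That needs a slope below 1. The slope is rho·s1/s0, and at s0/s1 of 0.25–0.30 it passes 1 once rho exceeds 0.25–0.30. The direction is not known for days smoked.
- *The DID serves no purpose beside the change score.* They coincide only with complete data. The article assumes 90% follow-up, and its missing-data section gives the DID a role as a likelihood-based method valid under MAR.

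It can also be said that the general covariate promise already covers baseline smoking, and that the Discussion plans site effects and adjustment for considerable imbalance. If baseline smoking were entered, the change-score model would indeed become the adjusted one. But the promise does not name it, the analysis section doubts that multi-covariate adjustment will be possible, and a covariate sentence does not repair a DID in which baseline is itself an outcome row.

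**Conclusion.** The outcome mismatch is established by the text alone: two sections name different outcomes for the same windows, and nothing links them. The modelling point also holds. Neither stated model contains a baseline-outcome term, and with complete data the DID adds no efficiency to the change score.

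The size of the gain is conditional. It is a variance ratio of 0.65–0.85, equivalent to 18–54% more participants (1/0.85 = 1.18, 1/0.65 = 1.54), if the SDs are equal and rho is 0.3–0.7. For days smoked it is 0.92–1.00 at rho 0.3–0.5 and 0.72–0.76 at rho 0.7, under assumed SD ratios of 0.25–0.30. These are large-sample results; at 36 per condition, estimating the slope can cancel a very small gain.

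A reader might infer that the trial's main result is at risk. It is not. Continuous abstinence and biochemically verified 7-day point prevalence are the named primary and secondary outcomes, the power statement concerns quit rates, and some analyses are declared to be mainly descriptive. This should be corrected, but it does not undermine the design.

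**What to change.** 1. Name the same reduction outcome in the analysis and Measures sections, or define both and rank them before data are seen. Cigarettes per day has the advantage of also capturing lower intensity on days still smoked; the choice belongs to the investigators.
2. For that outcome and every mediator measured at both times, model the follow-up value on condition, baseline value and site, allowing for clustering by counseling session. Alternatively, use a mixed model with baseline means constrained equal across conditions and an unstructured covariance for the two times. This keeps participants with missing follow-up under MAR.
3. Keep the DID as a sensitivity analysis, and drop the claim that it is the efficient estimator.

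The cost is wording plus about one degree of freedom per model for the baseline term. No new data are needed. Site terms are already planned, and an allowance for session clustering is needed whichever model is used, since the article itself assumes an ICC of 0.05.

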## Methods/design

### Overview

This pilot study involves a cluster cross-over randomized controlled design [32–34] with up to 80 current smokers who desire to quit and who are recruited from three drop-in centers serving young people experiencing homelessness in the Los Angeles area. Two of the drop-in centers are approximately a two mile drive from each other, with the third drop-in center being approximately a 10–15 mile drive from the others. The unit of analysis will be the individual, but individuals will be assigned to groups (standard care alone vs. TMI adjunct) based on the drop-in center where they are seeking services. All participants will receive standard care: a 30-min group-based smoking cessation counseling session and free nicotine replacement. Half of these smokers will then also receive the TMI, as an adjunct to this standard care, which will provide 6 weeks of ongoing text messaging support for quitting. This ongoing support includes continued and more intensive education regarding nicotine dependence, quitting smoking, and relapse; does not require additional agency resources; can be available “on demand” to the user; and includes features to personalize the quitting experience. During the field period, each drop-in center will alternate in delivering these two treatments, offering one group-based smoking cessation counseling session every other month (to reduce possible contamination between conditions), with the type of treatment delivered first at each drop-in center being randomly determined. This pilot study will investigate whether receiving the TMI adjunct to standard smoking cessation care results in greater reductions in cigarette smoking compared to standard care alone over a 3-month period.

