#### Power Considerations

A goal of this pilot study is to get an estimate of both the variability of the outcomes and of potential intervention effects so that we are better positioned to plan for the sample size for a future larger study [70]. To determine the necessary sample size for the larger study, we will determine what the clinically meaningful effects are for somewhat similar interventions from the literature. We will standardize such effects using the estimates of variability obtained with our pilot study data. For the pilot study, we plan to enroll up to 80 participants, with approximately 5–7 participants per group or cluster. We assume that 90% of them participate in the follow-up survey, based on our previous work [36], and assume a conservative interclass correlation (ICC) of 0.05. Under these assumptions, the effective sample size (ESS) at follow-up will be 36/(1 + 5*0.05) = 28.8 per condition. This provides 80% power to detect a moderate quit rate effect size (h = 0.72) for the difference between the two treatment conditions (alpha = 0.05).

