## Discussion

### Limitations and alternative methods considered

The proposed intervention focuses exclusively on cigarette smoking and is not designed to address the use of electronic nicotine delivery systems (ENDS), poly-tobacco use, or the co-use of tobacco with cannabis or other substances. However, we will be able to explore intervention effects on these other forms of substance use in our analyses. It should also be noted that we are not providing cell phones to participants while they participate in this study; rather, individuals must have a working cell phone that can receive text messages in order to participate. We will be monitoring the number of individuals who screen ineligible for this reason, or have a phone that is lost or stops working during the intervention, as indicators of the feasibility of using TMIs with this population.

In terms of the research design, we initially considered a design in which individuals would be randomly assigned to condition within agency. However, we decided against this design given concerns on the part of the research team and drop-in center staff about implementation challenges (e.g., clients perceiving that they were being refused services that other clients were getting) and the strong potential for contamination across conditions. A group-randomized design was a much better option for this evaluation in that it addressed both of these concerns. We will maximize the comparability of the intervention and control groups by: (1) having each drop-in center serve as both intervention and control site on an alternating basis; and (2) using the same procedures at each drop-in center to identify and recruit participants for the study. In addition, once the data are collected we will conduct preliminary analyses to determine whether the intervention and control groups differ on baseline characteristics. This step is necessary despite randomization because the randomization is not occurring at the individual level. If we observe considerable differences in the intervention and control groups, we will control for these with the addition of covariates into the regression models. We may also consider developing analytic weights using propensity score methods to balance the characteristics of the groups. As mentioned earlier, we will also control for any within-site effects by including site as a fixed effect (dummy coded) within the models.

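### The stated outcome models have no term for the counselling-session clusters that the design allocates and the power calculation adjusts for, so run as written they overstate precision

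*Protocol article*

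**What the plan says.** All references are to the protocol article.

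- **Allocation.** *Overview* and *Group counseling session and nicotine replacement* describe centres that alternate the two treatments from one counselling session to the next. *Preliminary analyses* says "participants will be randomly assigned (in groups of about 5–7 individuals"), so everyone in a session has the same condition.
- **Unit of analysis.** *Overview*: "The unit of analysis will be the individual".
- **Power.** *Power Considerations* says "we plan to enroll up to 80 participants, with approximately 5–7 participants per group or cluster". The authors "assume a conservative interclass correlation (ICC) of 0.05" and divide 36 per arm by 1.25, which gives an effective 28.8.
- **Models.** *Effects of the TMI on smoking behavior* names logistic regression for continuous abstinence (the primary outcome) and for 7-day abstinence. For smoking days it names a regression of the pre–post difference on arm, and a difference-in-differences (DID) model with "a random subject effect to properly account for the correlation of the repeated measures on each subject". *Effects of the TMI on other smoking-related outcomes* reuses the DID approach for the proximal outcomes.
- **Site.** *Limitations and alternative methods considered* adds: "we will also control for any within-site effects by including site as a fixed effect (dummy coded) within the models".

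No section names a session effect, GEE, a cluster-robust variance or a design-effect correction in the analysis.

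**The concern.** The power section treats the counselling group as a cluster whose members resemble one another. The analysis sections treat participants as independent once site, and in the DID model the participant, are accounted for. The stated power therefore belongs to a cluster-adjusted analysis that the analysis sections do not specify.

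Neither of the two dependence terms that are named reaches the right level. Condition varies between sessions within a centre. The site dummies absorb stable differences between three centres, above the session. The subject effect absorbs correlation between one person's two measurements, below it.

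What is at stake is the stated precision: confidence intervals for the intervention effect that are too narrow, and p-values that are generally too small. The purpose of the pilot is to show how large and how uncertain the effect may be before a larger trial.

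**Working it through.** **Inputs from *Power Considerations*.** Up to 80 enrolled, 90% followed up, ICC 0.05, 5–7 per cluster (the formula uses 6), h = 0.72, alpha 0.05. Sidedness is not stated; two-sided is assumed.

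**1. The plan's own figure.**
- Per arm: 80 × 0.9 / 2 = 36.
- Design effect (DE): 1 + (6 − 1) × 0.05 = 1.25. Effective size: 36 / 1.25 = 28.8, as stated.
- Two-sided power: Φ(0.72 × √(28.8/2) − 1.96) = Φ(2.732 − 1.96) = 78.0%, close to the stated 80%.

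**2. Effect of leaving the session out.** The true standard error is √DE times the model-based one. A nominal two-sided 5% test then runs at 2 × (1 − Φ(1.96/√DE)).
- At DE 1.25, √DE = 1.118. The naive standard error is too small by 1 − 1/1.118 = 10.6%, and the test level is 7.96%.

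| Session ICC | People per session | DE | Test level |
|---|---|---|---|
| 0.05 | 5 | 1.20 | 7.4% |
| 0.05 | 5.4 (6 less 10% loss) | 1.22 | 7.6% |
| 0.05 | 6 | 1.25 | 8.0% |
| 0.05 | 7 | 1.30 | 8.6% |
| 0.02 (assumed) | 6 | 1.10 | 6.2% |
| 0.01 (assumed) | 6 | 1.05 | 5.6% |

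**3. Do the site dummies repair it?** Simulation with no treatment effect: 12 sessions of 6 (72 analysed), four per centre, arms alternating, linear model, 20,000 replicates per case.
- All of the 0.05 at session level: 8.0% with site dummies, 7.9% without.
- Half stable site effect, half session: 6.5% with site dummies.
- All stable site effect: 5.0% with site dummies.

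Site dummies remove only the part of the correlation that belongs to the centre.

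**4. Logistic models.** Same layout, site dummies included, 6,000 replicates per case. The article gives no expected quit rate, so the rates are assumptions.

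| Quit rate | Wald, ICC 0 | Wald, ICC 0.05 | Likelihood ratio, ICC 0 | Likelihood ratio, ICC 0.05 |
|---|---|---|---|---|
| 10% | 1.3% | 2.7% | 7.1% | 9.9% |
| 20% | 4.7% | 7.0% | 5.8% | 9.1% |
| 30% | 4.9% | 8.1% | 5.7% | 9.0% |

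Clustering raises the level in every row. At a 10% quit rate, however, the Wald test starts so far below 5% that it stays conservative.

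**5. What a correct analysis costs.** The number of sessions is not stated; 80 / 6 gives about 13. A session-level regression with an intercept, condition and two site dummies leaves 13 − 4 = 9 df, for which t = 2.262.
- Interval width against naive: 1.118 × 2.262 / 1.96 = 1.29, or 29% wider.
- Power at h = 0.72: about Φ(2.732 − 2.262) = Φ(0.470) = 68%. The noncentral t distribution with 9 df also gives 68%.

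**The case against.** The strongest reply is that this is a pilot reported in a condensed article. Its stated aim is preliminary effect sizes. It warns that the sample may be too small for elaborate modelling and that some analyses will be mainly descriptive. No decision depends on p < 0.05, and details of variance estimation could sit in a fuller plan. The authors also clearly thought about grouping: they chose group allocation, adjusted the power for it and added site terms.

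Part of this stands. It limits the harm to the stated precision; no go/no-go rule is affected. It does not remove the point. The article does not leave dependence open: it names the subject effect and the site effect and omits the one level that its power section adjusts for. Descriptive intervals need a correct variance too.

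A reader might infer more than the documents support:

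- *That every p-value and interval is anti-conservative.* At an assumed 10% quit rate the Wald test is conservative.
- *That the effect handed to the larger trial is inflated.* Ignoring clusters understates uncertainty and does not by itself bias the estimate. *Power Considerations* also takes the target effect from the literature and uses the pilot for variability.
- *That 8% is a fixed figure.* It needs the whole ICC of 0.05 to remain at session level after site adjustment, and the authors call 0.05 conservative. That ICC was set for the quit-rate comparison; none is given for change scores.
- *That no session ICC could come from the pilot.* The stated models do not yield one, but nothing prevents estimating it, and the article does not promise one.

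**Conclusion.** The concern holds in this form: the outcome models, even with site dummies, omit the session clusters that the design allocates and the power calculation adjusts for. At the plan's own values, model-based standard errors would be about 10.6% too small and a nominal 5% test would run at about 8% (7.4–8.6% for 5–7 per session). The level falls to about 6.5% if half the ICC is a stable site effect, and to 5.6–6.2% at assumed session ICCs of 0.01–0.02. These figures assume a two-sided test. For the logistic models, which include the primary outcome, the exact level depends on the quit rate and on the test.

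The error is in precision, not in the point estimates. The power statement and the analysis section do not describe the same analysis and should be brought into line.

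**What to change.** - **All outcome models:** name the counselling session as the cluster and keep the site fixed effects.
- **Quit outcomes:** use a regression of session quit proportions on condition and site, or logistic GEE clustered on session with a small-sample-corrected variance and a t reference.
- **Continuous outcomes:** put a session random effect on the change score, or a session-by-time effect in the DID model, with a small-sample df correction. A plain session intercept in the DID model cancels from the change and would not help.
- **Reporting:** give the session ICC with its confidence interval, and say that about 13 sessions will estimate it imprecisely.
- **Power:** restate it for the analysis that will be run, about 68% at h = 0.72 with 9 df.

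This changes analysis wording only and needs no new data. The price is honest but not small: intervals about 29% wider than the naive ones, of which about 12% comes from the design effect (√1.25 = 1.118) and about 15% from the few degrees of freedom (2.262/1.96 = 1.154).
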